### Data and safety issues

#### Adverse events

At the 4-, 6-, and 8-month visits, participants are asked about any untoward medical events that have occurred since the prior visit, as well as emergency department visits and hospitalizations. Details of all adverse events are recorded and the study physician (AA) will assess each event for seriousness, severity, attribution, and preexisting status, and whether the participant’s continued activities in the trial should be modified or terminated. All adverse events are followed until resolution or the end of the participant’s follow-up period. All serious adverse events and unanticipated problems are reported according to IRB mandates, funding institute directives, and data and safety monitoring board (DSMB) requirements. Non-serious adverse events are reported to the local IRB annually and at all formal meetings of the DSMB.

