### Clinic procedures and assessment schedule

This trial includes a telephone screening call, an eligibility screening visit, a 1-month (31-day) run-in period, a randomization visit, then an 8-month follow-up period that includes four in-person visits. The content of each assessment is described below, and the timing described in the Spirit figure (Additional file 1; Fig. 2). The workflow of randomized participants is illustrated in Fig. 1.

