#### Intervention period

Participants randomized to the MBSR arm are registered to attend a public MBSR class. In most cases, there is a waiting period of up to 3 months before the class begins. The 8-month follow-up period begins on the official first MBSR class date. Participants have the option to conduct the intervention-period study visits virtually.

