#### Follow-up visits

Three months after the start of the MBSR classes, participants attend for a follow-up visit and are asked to wear the actigraph again for 14 days. We collect any feedback on the MBSR class for those in the intervention arm. The second headache diary (for measurement of the primary study outcome) is provided.

Four months after the start of the MBSR classes, participants attend for a follow-up visit. They return their actigraph and the second headache diary, and complete the online questionnaires. They are also asked about any adverse events.

Six months after the start of the MBSR classes, participants attend for a follow-up visit. They return their third headache diary and complete the online questionnaires. They are asked about any adverse events.

Eight months after the start of the MBSR classes, participants attend for a follow-up visit. They return their fourth and final headache diary and complete the online questionnaires. They are asked about any adverse events. Participants in the control group are offered the MBSR course, and all participants are asked if they would be willing to take part in a focus group.

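### The 4-month adverse-event question looks back only to the preceding visit, so read literally no stated window covers the MBSR course or the wait before it

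*Protocol article*

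**What the plan says.** All places are in the protocol article.

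- **Adverse events** fixes both the timing and the recall period: "At the 4-, 6-, and 8-month visits, participants are asked about any untoward medical events that have occurred since the prior visit". The same sentence adds emergency department visits and hospitalizations. It is not clear whether the look-back applies to those as well.
- **Clinic procedures and assessment schedule** describes "an 8-month follow-up period that includes four in-person visits".
- **Follow-up visits** names the four as months 3, 4, 6 and 8. On the first it says: "Three months after the start of the MBSR classes, participants attend for a follow-up visit and are asked to wear the actigraph again". The other items listed at month 3 are handing out the second headache diary and, in one arm only, class feedback: "We collect any feedback on the MBSR class for those in the intervention arm". No adverse-event question is listed there.
- **Follow-up visits** does list an adverse-event question at months 4, 6 and 8. At month 4 it reads: "They are also asked about any adverse events". No recall period is attached.
- **Intervention period** starts the follow-up clock at the first MBSR class and says that in most cases "there is a waiting period of up to 3 months before the class begins".

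**The concern.** A look-back to the preceding visit works only if every visit carries the question, or if the first window is given its own start date. Here the month-3 visit lies between the course and the first adverse-event question, and no start date is stated. A coordinator who follows the Adverse events section to the letter would ask at month 4 about the previous month only. Anything that happened during the classes, or while waiting for them, would be left to spontaneous report.

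The data at stake are those from the time when participants are exposed to the intervention. The Data and safety section puts safety data in the reports to the monitoring board. The Discussion says the pilot is meant to rehearse the essential elements of the full trial, so an undefined window could be carried into that trial.

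**Working it through.** The plan states no coverage figure to reproduce. The check is timeline arithmetic, with month 0 at the first class and 1 month = 30.44 days.

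**Inputs**
- Follow-up: 8 months from the first class (Intervention period; Clinic procedures and assessment schedule).
- Visits: months 3, 4, 6 and 8 (Follow-up visits).
- Adverse-event questions: months 4, 6 and 8, each looking back to the preceding visit (Adverse events).
- Course length: 8 weeks (Abstract, Methods/design).
- Wait W from randomization to class: 0 to 3 months (Intervention period).

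**Step 1. Where the course lies.** 8 × 7 = 56 days, and 56 / 30.44 = 1.84 months. Month 3 is 3 × 30.44 = 91 days. The weekly course is over about 35 days before the month-3 visit.

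**Step 2. Literal windows.** The visit before month 4 is month 3, the one before month 6 is month 4, and the one before month 8 is month 6. The windows are months 3–4, 4–6 and 6–8.
- Covered: 1 + 2 + 2 = 5 of 8 months = 62.5%.
- Not covered: 3 of 8 months = 37.5%, which includes all 8 course weeks.

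**Step 3. Counting from randomization.** Share not covered = (3 + W) / (8 + W).

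| Wait W (months) | Not covered | Share |
|---|---|---|
| 0 | 3 of 8 | 37.5% |
| 1 | 4 of 9 | 44.4% |
| 2 | 5 of 10 | 50.0% |
| 3 | 6 of 11 | 54.5% |

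**Step 4. Other readings.** If the preceding visit means the randomization visit, or if the open wording in Follow-up visits governs, the month-4 question reaches back over the course. Coverage from class start is then 8 of 8 months, and there is no gap.

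**Step 5. Recall length if the window starts at randomization.** The first recall period is 4 + W months when asked at month 4, so 4 to 7 months. It is 3 + W months when asked at month 3, so 3 to 6 months.

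The same text thus gives anything from 62.5% to 100% coverage of follow-up, depending on which section staff follow.

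**The case against.** The strongest reply is that Follow-up visits describes the month-4 question without any limit. The Adverse events sentence names only months 4, 6 and 8, so the visit before month 4 in that series could be the randomization visit, the last time questionnaires were completed. On either reading the course is covered. The article also condenses a fuller protocol, and its schedule figure is not shown. Serious events and unanticipated problems have a reporting route that is not worded as confined to the scheduled questions. The trial is a feasibility pilot of about 60 people, with no safety endpoint and no planned comparison of event rates.

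Most of this stands, and it limits the conclusion. It does not remove the defect. The Adverse events section gives the only recall period in the document, and Clinic procedures and Follow-up visits both count month 3 as a visit. If the preceding visit means the last one with an adverse-event question, none exists before month 4, so the window has no defined start. The serious-event route says where events are reported, not how they are found before month 4. The complaint is not about omitted detail: the article states a rule, and the rule conflicts with its own schedule.

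A reader might also infer that a window from randomization would bias event counts against MBSR, at 4–7 months against 4 in controls. That requires controls to be timed from randomization. Study intervention gives them a schedule identical to the MBSR arm's, while the Discussion already discloses differential follow-up periods and defers the remedy to the full trial. The article settles neither the control clock nor any comparison of crude counts, so that bias is not shown.

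**Conclusion.** The point holds as a badly fixed recall window and a conflict between two sections. Followed as written, the Adverse events rule leaves 3 of 8 follow-up months, including the entire 8-week course, outside every stated window. With the longest stated wait, 6 of 11 months after randomization are uncovered. These figures rest on two assumptions: that the preceding visit means month 3, and that no adverse-event question is asked there, as the article's text indicates.

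A reader might infer that events during the course are never elicited. The documents do not support that, because the open wording in Follow-up visits allows the month-4 question to cover the course. What was actually asked cannot be known from this article. The correction is still worth making: the rule concerns safety data from the exposure period, and the remedy costs almost nothing.

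**What to change.** 1. State that the first question on adverse events, emergency visits and hospitalizations looks back to randomization, and that each later one looks back to the last adverse-event assessment. Use the same wording in Adverse events and Follow-up visits.
2. Ask that first question at month 4, or at the existing month-3 visit. If month 3 is used, ask it in both arms, since the class feedback collected there comes from the intervention arm only.
3. Ask participants still in follow-up once, at their next contact, for the whole period since randomization. Trial status gives 21 September 2018 as the end of recruitment. If the last participant was randomized about then, a 3-month wait plus 8 months runs to about August 2019.
4. Because time since randomization can vary with the class wait, show person-time at risk by arm beside any event counts.

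The cost is a reworded question, a small amendment and, if month 3 is used, one more form at an existing visit. The main drawback is a longer first recall period (up to 7 months at month 4, or 6 at month 3), with some loss of accuracy for minor events. Asking at month 3 shortens it.

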#### Data and safety

A DSMB is constituted for this pilot trial, consisting of one experienced clinical trialist, a migraine clinician/content expert, and a statistician. Both blinded and unblinded data are provided, per the determination of the DSMB. The meeting schedule and content of the DSMB reports are consistent with the guidelines of the funding institute and will be modified and approved as necessary by the DSMB itself. The content of the DSMB reports consists of all relevant trial progress information, safety data, and measures of data completeness and quality.

## Discussion

Migraine headaches are one of the most common neurological conditions seen in primary and specialty neurological care. They are often distressing. Despite the availability of several effective preventive and rescue medications, many patients continue to suffer with migraine symptoms as these therapeutics are insufficiently effective for many patients, are often associated with bothersome side effects, and can be very expensive. In addition, many patients prefer interventions that do not involve medications and over which they have control [31].

MBSR has been shown to provide clinically meaningful benefits with few adverse effects for patients with a wide variety of chronic-pain syndromes such as chronic low back pain [32–34] and fibromyalgia [35, 36], among other conditions. To date, however, there are no results from large-scale fully powered clinical trials of an MBSR intervention for patients with frequent migraine headaches. Research into the clinical and biological effects of stress-altering interventions is in the early stages. One small pilot trial (*N* = 19) found an indication of potential clinical benefits of MBSR [11]. Two additional trials of MBSR among migraine patients are also in progress, including one trial with clinical outcomes and another on cross-sectional imaging outcomes (https://clinicaltrials.gov/ct2/show/record/NCT02695498 and https://clinicaltrials.gov/ct2/show/record/NCT02133209).

Such a trial would require substantial resources and patient commitment. Prior to embarking on such an endeavor, it is prudent to ensure that study methods are robust and will likely lead to a successful, valid phase III clinical trial.

This protocol describes a pilot trial to compare the effect of community-based MBSR classes with usual care to usual care alone as a preventive treatment for patients with moderately severe migraine headaches. The trial is designed to be highly pragmatic, recruiting a community-based sample of participants with few restrictions on adjunctive therapies and using community-based MBSR classes that represent the typical experience of patients who might choose to practice MBSR for migraine prevention. Thus, the patient population and the intervention are likely to be representative of the usual clinical environment in which such an intervention would be offered. Generalizability is also enhanced by the inclusion of multiple independent recruitment strategies, allowing for comparison of alternative recruitment approaches. The study includes a wide range of clinically relevant outcomes and includes a test of the feasibility of digital-sensor technology (actigraphs) to give a better understanding of the physiological responses to an MBSR intervention.

Note that there are several limitations to our approach for this pilot study. First, because we do not have an active comparison arm or attention control, the participants cannot be blinded to their treatment. There may be non-specific or placebo effects associated with the treatment, which we do not want to lose in an analysis of the effectiveness data in a fully powered trial [37]. We did not include measures of expectancy. These should be included in a fully powered trial since they may shed light on observed responses. We accept a clinical diagnosis of migraine for eligibility and did not include a baseline validation by a neurologist or headache specialist. We have also discovered that the time between randomization and intervention-group participants starting their MBSR classes was longer than expected (often several weeks), introducing an imbalance and potential bias from differential follow-up periods. This problem will require a design change in a fully powered study (such as matching follow-up periods for intervention and control participants). We also did not collect detailed data on all potential co-interventions in the control group nor the characteristics of the classes in the intervention group. Finally, we did not include any interventions to promote adherence to the home diary collection. As adherence was a feasibility outcome for this study, if we learn that adherence to completing the diaries is suboptimal, we will include reminders in the fully powered trial.

This pilot trial was designed to replicate, on a limited scale, all of the essential elements of a fully powered effectiveness study of MBSR for patients with migraine, including recruitment, run-in, randomization, application of the intervention, data collection (including all patient-reported outcomes and mechanistic studies), adherence monitoring, retention, study closeout, and regulatory compliance (including a fully constituted DSMB). Lessons learned in this pilot study will be incorporated into the design of future phase III studies. The results of this pilot study will inform future studies of MBSR for migraine and other related conditions, helping ensure that future studies of this promising intervention are valid and generalizable to usual clinical settings.

### Trial status

This trial is registered at clinicaltrials.gov (NCT02824250; https://clinicaltrials.gov/ct2/show/NCT02824250), and was first posted on 6 July 2016. The first participant gave their consent on 2 February 2017 and was randomized on 9 March 2017. Recruitment was completed 21 September 2018. The most recent version of the protocol (V2.0) was approved by the Sutter Health IRB on 9 March 2018 (Sutter IRB #: 2016.070EXP IRBNet #: 897613).

## Abbreviations

DSMB: Data and safety monitoring board
EHR: Electronic health records
HIT: Headache Impact Test
IRB: Institutional review board
M&M: Mindfulness and Migraine
MAAS: Mindful Attention Awareness Scale
MBSR: Mindfulness-based stress reduction
MIDAS: Migraine Disability Assessment
MSQ: Migraine-specific quality of life
NIH: National Institutes of Health
NINDS: National Institute of Neurological Disorders and Stroke
PROMIS: Patient-reported Outcomes Measurement Information System
PSS-10: Perceived Stress Scale
REDCap: Research electronic data capture
SF-12: Medical Outcomes Study Short Form 12
WPAI: Work Productivity and Activity Impairment
